## Abstract

Supplemental Digital Content is available in the text

## Introduction

1

Primary hypertension is a disease characterized by persistent high blood pressure without identifiable causes; it affects 31.1% of adults worldwide and is a chief cause of cardiovascular events and premature death.^[1]^ It is well established that blood pressure-lowering treatment can improve the prognosis of hypertension.^[2,3]^ However, the effectiveness of the mainstay of hypertension treatment, antihypertensive drugs, is always limited by side effects and poor compliance.^[4]^ Some studies even suggest that antihypertensive drugs are associated with increased risks of hip fracture and cancers (eg, skin cancer).^[5,6]^ Therefore, efforts are increasingly being made to research new management approaches for hypertension.

The efficacy of acupuncture and moxibustion for the treatment of hypertension has been suggested by a network meta-analysis of randomized controlled trials, in which moxibustion was shown to be more effective than acupuncture, although the evidence was of low quality.^[7]^ Moxibustion is an acupoint stimulation therapy that applies heat stimulation to specific acupoints by burning moxa.^[8]^ The antihypertensive mechanism of moxibustion is still uncertain. It is hypothesized that heat stimulation by moxibustion can result in the regulation of vasodilatation and cardiac rhythm, with mediators such as histamine, plasma aldosterone, and atrial natriuretic peptide; these effects, combined with the effects of the aroma and psychological relaxation experienced during moxibustion treatment, ultimately decrease blood pressure.^[9–11]^

Heat-sensitive moxibustion, an innovative acupoint stimulation therapy, has been developed based on traditional moxibustion in recent decades.^[12]^ The major innovation in heat-sensitive moxibustion therapy is the discovery of heat-sensitive acupoints.^[13]^ Researchers find that when persons suffer from diseases, heat-sensitive points appear on their body, and these points may differ from the classic acupoints in terms of location. When moxibustion is applied to heat-sensitive acupoints, patients experience unusual feelings (referred to as “heat-sensitive sensations”), including penetrating heat, expanding heat, heat transfer, distant heat, deep heat, and other feelings unrelated to heat (such as soreness, bloating, and numbness).^[12]^ It has been proven that heat-sensitive moxibustion is more efficacious than traditional moxibustion for multiple diseases, such as lumbar disc herniation and bronchial asthma.^[14,15]^

In principle, heat-sensitive moxibustion should be effective for hypertension. However, there is no high-quality evidence regarding the effects of heat-sensitive moxibustion on hypertension to date, and all current evidence regarding other acupoint stimulation therapies, including traditional moxibustion for hypertension, was generated in a hospital setting. For a chronic disease such as hypertension, compliance with treatment will be poor if patients are required to go to the hospital regularly to receive acupoint stimulation therapy. In contrast, patients can administer moxibustion treatment to themselves or with the help of their family at home after receiving brief training. Therefore, we assume that heat-sensitive moxibustion may be a feasible approach to the management of hypertension in a community setting. To verify this hypothesis, we will conduct a nonrandomized controlled study in multiple communities to evaluate the pragmatic effectiveness and safety of heat-sensitive moxibustion self-administration in patients with primary hypertension.

## Methods and analysis

2

### Study design

2.1

This is a multi-center, pragmatic, nonrandomized study that is registered in Clinicaltrials.gov (ID: NCT04381520) on May 11, 2020. This protocol (version 1.0) was developed according to the Standard Protocol Items: Recommendations for Interventional Trials (SPIRIT) checklist.^[16]^

### Site and participant recruitment

2.2

We will recruit patients with primary hypertension from 4 communities: the Nangang community, the Honggutan community, the Shengmi community in Nanchang city, and the Gaofu town community in Fu Zhou city. Recruitment will occur through community doctors’ oral communication with individuals, posters, and mobile advertising. Patients who express a preliminary willingness to participate in the study will be screened for eligibility and informed about the entire study process, benefits, and potential harms. Eligible patients will formally enter the study cohort after signing the informed consent form. The overall study design is shown in Figure 1.

**Figure 1 F1:**
[figure not shown]
Flowchart of the study.

### Eligibility criteria

2.3

A patient will be eligible to participate in this study if he or she has been diagnosed with primary hypertension according to American College of Cardiology/American Heart Association criteria (ie, systolic blood pressure [SBP] ≥ 130 mm Hg or diastolic blood pressure [DBP] ≥ 90 mm Hg),^[17]^ is between 18 and 70 years old and is willing to sign the informed consent form. However, the following patients will be excluded:

(1)patients with hypertension secondary to pregnancy; brain, macrovascular, kidney or endocrine disease; or drug-induced factors;(2)patients who are allergic to moxa, moxa smoke, or the moxibustion device;(3)patients who are pregnant or lactating;(4)patients who have experienced serious cardiovascular and cerebrovascular events (eg, myocardial infarction and stroke);(5)patients with other severe diseases, such as liver and kidney dysfunction indicated by a level more than 2 times the upper limit of normal for total bilirubin, alanine aminotransferase, aspartate aminotransferase or serum creatinine; malignant tumors; and major mental disorders.

### Training and assignment

2.4

There is a community health service center in each community. Before the study begins, we will invite senior experts to give 4 lectures (once per week) for residents in each community health service center to introduce the principal and anticipated efficacy of the use of heat-sensitive moxibustion for the management of hypertension. After fully comprehending the relevant knowledge, eligible patients will enter the heat-sensitive moxibustion group or the control group according to their preferences. Investigators and community doctors will not provide any advice regarding the group selection. For patients entering the heat-sensitive moxibustion group, community doctors will further provide one-on-one training, explaining how to perform heat-sensitive moxibustion, how to identify heat-sensitive acupoints, and how to avoid burns, among other safety precautions.

### Interventions and co-interventions

2.5

Patients in the heat-sensitive moxibustion group will self-administer heat-sensitive moxibustion for one year while maintaining their original antihypertensive drugs. With the doctors’ help, the patients will first identify the heat-sensitive acupuncture points near CV8 (Shenque, the center of the navel), CV4 (Guanyuan, approximately 10 cm below the navel), and bilateral ST36 (Zusanli, approximately 7 cm below the lateral of the knee) and then perform moxibustion on the heat-sensitive acupoints. Self-sticking mini-moxa rolls will be used as the combustible material, which can be placed and burned in a moxibustion box (Fig. 2). A matching velvet bag can be used to wrap the moxibustion box to avoid burns. The suggested dose of moxibustion will be one moxa roll (approximately 30 minutes) per session, with 1 session per day and 7 sessions per week. Driven by a pragmatic design, we will allow the patients to adjust the dose of moxibustion to make it convenient, but they need to truthfully report the adjusted dose. Patients in the control group will only maintain their original antihypertensive drugs and will not perform heat-sensitive moxibustion. There will be no restriction on the type and dose of antihypertensive drugs, but other acupoint stimulation therapies, such as acupuncture, will be prohibited.

**Figure 2 F2:**
[figure not shown]
Schedule of study visits. FBG = fasting blood glucose, HbA1c = hemoglobin A1c, TC = total cholesterol, TG = triglycerides, HDL-C = high density lipoprotein cholesterol, LDL-C = low density lipoprotein cholesterol, Scr = serum creatinine.

### Outcome

2.6

#### Primary outcomes

2.6.1

(1)Changes in SBP and DBP (mm Hg) measured with an electronic sphygmomanometer. The average value of 3 measurements will be used.(2)Percentage changes in the dose of antihypertensive drugs. At each regular visit, the community doctors will determine whether the dose of antihypertensive drugs needs to be adjusted according to changes in blood pressure during the last month and will record the adjustment.

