### Study visits

2.8

During the 1-year follow-up period, the investigators will visit the patients monthly at the community health service centers, which are generally within 1 km of the patients’ homes. At month 0 (baseline visit), we will collect demographic characteristics (name, phone number, sex, age, education level, height, and weight) and disease-related characteristics (SBP, DBP, course of hypertension, comorbidities, smoking, drinking, and type and dosage of antihypertensive drugs currently used). At months 6 and 12, we will measure blood pressure, changes in doses of antihypertensive drugs, quality of life, blood and urine indicators, and AEs. The other regular visits (ie, months 1–5 and 7–11) will involve the distribution of moxa rolls and moxibustion boxes to patients, the assessment of patient compliance and the adjustment of the doses of antihypertensive drugs. A detailed schedule of the study visits is shown in Figure 2.

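### The primary blood pressure reading is not timed against the moxibustion session and the interval is not recorded, so a short-lived post-session fall could be counted as a sustained effect

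*Protocol article*

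**What the plan says.** Section 2.6.1 gives the measurement rule for systolic and diastolic pressure as "measured with an electronic sphygmomanometer. The average value of 3 measurements will be used". It specifies device and averaging, but neither time of day nor time since treatment.

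Section 2.8 places the follow-up measurements at two visits to the community health service centre: "At months 6 and 12, we will measure blood pressure". The centres are generally within 1 km of patients' homes.

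Section 2.5 suggests a daily home session, "one moxa roll (approximately 30 minutes) per session, with 1 session per day and 7 sessions per week", and adds that "we will allow the patients to adjust the dose of moxibustion to make it convenient". The clock time of a session is left to the patient. For the comparison group, "Patients in the control group will only maintain their original antihypertensive drugs and will not perform heat-sensitive moxibustion", and there is no sham session.

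On mechanism, the Introduction hypothesises that "heat stimulation by moxibustion can result in the regulation of vasodilatation and cardiac rhythm", and that "these effects, combined with the effects of the aroma and psychological relaxation experienced during moxibustion treatment, ultimately decrease blood pressure". It also says that the mechanism is uncertain.

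The covariates and subgroups in section 2.12 do not include time since the last session.

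**The concern.** The treated patients' follow-up readings can fall at any interval after a session. One patient may treat just before a short walk to the centre, and another the evening before. If a session lowers pressure for a short while, the first patient is read inside that window and the second is not.

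Such a fall has no counterpart elsewhere in the comparison. At baseline no trial session has taken place, and controls who follow their assignment have none at any visit. It would therefore remain in the between-group difference in change from baseline. Averaging three readings from one visit would not remove it, because all three share the same interval since treatment.

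This matters for the claim that the study wants to make. The Discussion looks towards a long-term therapy that might take over part of the role of antihypertensive drugs. Support for that requires pressure that stays lower between sessions. If the interval is not recorded at the visit, the analysis cannot separate a sustained effect from a passing one, and the information cannot be recovered reliably later.

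**Working it through.** **No plan figure to reproduce on this point.** The article states no size or duration for a post-session fall, and no share of patients treating shortly before a visit. The check has two parts: whether the text leaves the gap open, and what the gap could do under stated assumptions.

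**1. The text, side by side**

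| Question | Where | Answer |
|---|---|---|
| How is the reading taken? | 2.6.1 | Electronic device, mean of 3 |
| When, after baseline? | 2.8 | Months 6 and 12 |
| Interval since session fixed? | 2.5, 2.6.1, 2.8 | No |
| Clock time of session recorded? | 2.5, 2.8, 2.9 | No; only the dose used is reported and checked |
| Adjusted for in analysis? | 2.12 | No |
| Is an acute effect plausible on the plan's own rationale? | 1 | Yes, as a hypothesis |

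**2. Bias under assumptions**

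Mean bias b = p × f, where p is the share of treated patients read soon after a session and f is the short-lived fall in those patients. Both are assumed.

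- p = 10%, f = 5 mm Hg: b = 0.10 × 5 = 0.5 mm Hg, which is 10% of the 5 mm Hg expected in section 2.11.
- p = 50%, f = 5 mm Hg: b = 0.50 × 5 = 2.5 mm Hg, which is 50% of it.

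**3. What that would do to the test if there were no sustained effect**

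Inputs from section 2.11: SD 20 mm Hg, 300 per group, 20% attrition, alpha 0.05 (taken as two-sided). Completers per group = 300 × 0.80 = 240.

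SE of the difference = 20 × √(2/240) = 1.83 mm Hg.

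Probability of a significant result = Φ(b/SE − 1.96) + Φ(−b/SE − 1.96).

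- b = 0.5: 5.9%.
- b = 2.5: 27.8%.

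These use an unadjusted two-group comparison and ignore confounding from the preference-based assignment. They illustrate the effect and do not estimate it.

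**4. A separate matter.** The minimum of 140 per group in section 2.11 does not follow from its inputs. Two-sided, 2 × (20 × (1.960 + 0.842)/5)² gives 252 per group, and 252/0.80 = 315. The timing point does not depend on this.

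**The case against.** **An article need not state every reading condition.** Section 2.10 mentions training in standard procedures and pilot-tested case report forms, and the visit schedule in Figure 2 is not shown. A timing rule may exist there. This stands as a caveat. However, the article does set out how the primary reading is taken, and nothing in it points to such a rule.

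**The mechanism does not establish a short-lived fall.** The Introduction calls it uncertain, also names hormonal mediators, and describes relaxation during treatment without saying how long any fall lasts. This is correct: the text makes an acute effect plausible and no more.

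**Readings under ordinary use are a legitimate pragmatic target, and a pre-session reading may understate the day's average.** There is something in this. But one reading at an unrecorded interval does not estimate the day's average either, and the Discussion's aim concerns lasting control.

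**Fasting blood tests at months 6 and 12 suggest early visits in both groups.** That may narrow the clock time, but it does not prevent a session that morning.

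**The asymmetry is not absolute.** Section 2.12 foresees controls who perform moxibustion and treated patients who stop. Both would dilute the difference without removing it.

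**Stronger readings that the documents do not support.**

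- A reader might infer that the bias amounts to 25% to 100% of the expected effect. That follows from assuming 25% × 5 = 1.25 mm Hg up to 50% × 10 = 5 mm Hg. Neither factor is in the article, and the upper case assumes a passing fall twice the whole expected effect.
- A reader might also infer that the same readings drive the second primary outcome, the change in drug dose. Section 2.6.1 bases that decision on blood pressure changes over the preceding month, and section 2.8 also schedules it in months when no outcome reading is listed. Overlap is possible at months 6 and 12 only.

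**Conclusion.** The point holds as a gap in the definition of the primary measurement. It does not show that the result will be biased. As the article states it, the month 6 and 12 readings may fall at any interval after a session whose time the patient chooses, and that interval is not captured. A short-lived fall, if there is one, would favour moxibustion.

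The size cannot be determined from the documents. Under the two assumed cases it is 0.5 or 2.5 mm Hg against an expected 5 mm Hg, so it could be negligible or it could matter. The conclusion assumes that a post-session fall exists, that some patients treat shortly before a visit, and that no procedure outside the article already controls the timing.

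The change should be made because it costs almost nothing and the missing information cannot be rebuilt at analysis.

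**What to change.** In section 2.6.1, add that the month 6 and month 12 readings are taken before that day's moxibustion session. They should fall in the same part of the day as the patient's baseline reading, with the same time-of-day rule in both groups. Record the clock times of the reading and of the last session. If an operating procedure already says this, state it in the outcome definition.

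In section 2.12, keep all readings in the primary intention-to-treat analysis, including those from patients who have already treated that day. Excluding them would remove patients from essentially one group on the basis of behaviour after baseline, which adds selection to a comparison that is already nonrandomised. Instead, report the effect by time since last session as a descriptive sensitivity analysis, and note that this time is itself a post-baseline behaviour.

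The cost is one line in the visit reminder and two time fields on the case report form. The sample size does not change. The downside is that some patients will move that day's session until after the visit.

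### The primary outcome of percentage change in drug dose has no value for patients untreated at baseline, and no common scale when drugs are added or switched

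*Protocol article*

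**What the plan says.** - **Outcome (section 2.6.1).** There are two primary outcomes: "Changes in SBP and DBP (mm Hg) measured with an electronic sphygmomanometer", and "Percentage changes in the dose of antihypertensive drugs". For the second, community doctors decide at each regular visit "whether the dose of antihypertensive drugs needs to be adjusted according to changes in blood pressure during the last month" and log any change. The article gives no dose scale and no rule for the denominator.
- **Eligibility (section 2.3).** "A patient will be eligible to participate in this study if he or she has been diagnosed with primary hypertension", with the threshold given as "systolic blood pressure [SBP] ≥ 130 mm Hg or diastolic blood pressure [DBP] ≥ 90 mm Hg", plus age 18 to 70 and consent. None of the five exclusions concerns patients who take no antihypertensive drug.
- **Background drugs (section 2.5).** "There will be no restriction on the type and dose of antihypertensive drugs". The same section has both groups stay on the drugs they entered with.
- **Visits (section 2.8).** Drug type and dosage are recorded at baseline. "At months 6 and 12, we will measure blood pressure", together with dose changes. Dose adjustment is listed for months 1 to 5 and 7 to 11.
- **Analysis (section 2.12).** Primary outcomes are analysed by intention to treat. The adjusted model includes baseline SBP and drug types as dummies. Baseline dose is not among the covariates.

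**The concern.** A percentage change needs a non-zero baseline and one unit of measurement. The eligibility criteria do not secure the first, and unrestricted drug types do not secure the second.

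An untreated patient has no value whatever happens later. A treatment start, which is an increase in drug use, leaves no trace in the outcome. The excluded patients are defined by a baseline characteristic, and patients choose their own group (section 2.4), so the untreated share may differ between groups. The plan to decide on imputation later does not help. These values are not missing; they do not exist.

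Dose is also adjusted in response to blood pressure, so the two primary outcomes are linked. A difference in drug use can be read only beside the pressure achieved on it, and the reverse. The article states no joint reading.

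**Working it through.** **Plan's own figure.** There is none for the dose outcome. The sample size in section 2.11 is based on SBP alone and does not bear on this point.

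**Step 1: zero baseline.** Percentage change = 100 × (follow-up − baseline) / baseline.
- Untreated, then 5 mg of a drug: 100 × (5 − 0) / 0, undefined.
- Untreated throughout: 100 × (0 − 0) / 0, undefined.

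An equivalence scale does not cure this, because zero in any unit is still zero.

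**Step 2: added or switched drugs, on raw milligrams.** Drugs and doses are hypothetical.
- Switch from 5 mg of A to 80 mg of B: 100 × (80 − 5) / 5 = +1500%.
- Add 12.5 mg of C to 5 mg of A, summed: 100 × (17.5 − 5) / 5 = +250%.
- The same addition drug by drug: A is 100 × (5 − 5) / 5 = 0%; C is undefined.

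The result depends on an unstated convention, and the milligram figures say nothing about the amount of treatment.

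**Step 3: the same cases on an absolute load.** Load = sum over drugs of (daily dose / fixed standard daily dose). Take 5, 80 and 12.5 mg as purely illustrative standard doses for A, B and C.
- Start of A: 0 to 5/5 = 1, change +1.
- Switch from A to B: 5/5 = 1 to 80/80 = 1, change 0.
- Addition of C: 1 to 5/5 + 12.5/12.5 = 2, change +1.

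Every case has a value.

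**Step 4: size.** Inputs from section 2.11: 300 per group and 20% attrition, so 300 × 0.80 = 240 followed per group. The untreated share u is not in the article and is assumed. Undefined among those enrolled = 600 × u; evaluable per group = 240 × (1 − u). The article gives no effect size for dose, so power is shown for an assumed standardised effect of 0.25 (borrowed from 5/20 for SBP), two-sided α = 0.05, normal approximation: Φ(0.25 × √(n/2) − 1.96).

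| Assumed u | Undefined of 600 | Evaluable per group | Power |
|---|---|---|---|
| 0% | 0 | 240 | 78% |
| 10% | 60 | 216 | 74% |
| 20% | 120 | 192 | 69% |
| 30% | 180 | 168 | 63% |
| 50% | 300 | 120 | 49% |

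The loss of power is secondary. The main harm is that a group defined at baseline, and every treatment start in it, is left out of a primary outcome.

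**The case against.** The article speaks of patients' existing drugs and codes drug types in the model, which presumes that most patients are treated. The affected share could therefore be small. That stands as a limit on size, but presuming treatment is not an eligibility criterion.

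An equivalence scale for treated patients who add or switch drugs may sit in a full protocol or analysis plan that is not shown. That also stands: with such a scale, those patients have a valid percentage. It does not reach patients with a zero baseline.

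A reader might go further in three ways that the article does not support.
- **That a dose cut alone counts as success, even with higher pressure.** No section states such a rule. The Discussion mentions partial replacement of drugs, but only on condition that efficacy is shown, and blood pressure is the first-listed primary outcome.
- **That the monthly readings behind dose decisions are absent from the data set.** Section 2.8 refers to Figure 2 for the detailed schedule, and that figure is not available here.
- **That dose adjustment would mask a true SBP effect by a known amount.** An assumed offset of 20% to 50% would leave 5 × 0.80 = 4 to 5 × 0.50 = 2.5 mm Hg, with SBP power at 240 per group falling from 78% to 59% and 28%. The article gives no offset, and these figures describe SBP, not the dose outcome. SBP under usual dose adjustment is also a legitimate target in a pragmatic study, and having both outcomes primary is a reasonable response to the link between them.

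**Conclusion.** The definition needs correcting. For a patient untreated at baseline the outcome is undefined by arithmetic, the eligibility criteria admit such patients, and no later analysis document can repair this while the measure stays a percentage. That conclusion needs no assumption. For added or switched drugs the conclusion is weaker: no meaningful percentage without an equivalence scale, which may exist elsewhere.

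The number affected is unknown. The counts of 60 to 300 of 600 rest entirely on assumed untreated shares of 10% to 50%.

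Section 2.5, where both groups keep their original drugs, conflicts with sections 2.6.1 and 2.8, where doses are adjusted at regular visits. These must be reconciled, because a dose-change outcome depends on which applies.

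**What to change.** 1. Redefine the outcome in section 2.6.1 as change from baseline in total daily drug load: each drug's daily dose divided by a fixed standard daily dose, summed over drugs, zero if untreated.
2. Analyse it in all intention-to-treat patients by analysis of covariance, adding baseline load to the covariates in section 2.12.
3. Add an ordinal sensitivity analysis (decreased, unchanged, increased), with treatment starts and added drugs counted as increased.
4. Report the load difference with the SBP and DBP differences at the same visit, and state that neither drug load nor blood pressure is interpreted alone. Months 6 and 12 already collect both.
5. Reconcile section 2.5 with sections 2.6.1 and 2.8 on whether drug doses are held or adjusted.

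**Cost.** Revised wording and a drug conversion table fixed before analysis. The load uses drug type and dosage recorded at baseline and the adjustments already logged. The downside is a result less intuitive than a percentage. A repeated-measures model of monthly blood pressure is not proposed, because those readings also reflect earlier dose changes and the model would not remove that effect.

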### Data management and monitoring

2.10

All investigators will receive training in standardized operating procedures before the study starts. Data will be collected by community doctors using pilot-tested case report forms. Each patient's informed consent form and case report forms will be bound into 1 volume for management. The distribution of the moxa rolls and moxibustion boxes will also be strictly recorded. The software used to manage the electronic database will be Microsoft Access version 2016 (Microsoft Corporation, US), and the data will be doubly input and cross-checked by 2 independent investigators. All data in the database will be anonymized. When performing data analysis, the grouping will be concealed from the analysts.

An independent data monitoring committee will be established to monitor the quality of the data collection (eg, whether there are any incorrectly reported or missing data) and to ensure that any amendments or incomplete data are addressed in a timely manner. The committee will also have the right to plan an interim analysis (eg, when all patients have completed 6 months of follow-up) and to decide whether to discontinue the study based on the efficacy and safety results of the interim analysis.

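### The drug-dose primary outcome is a treatment decision made and recorded by doctors who know the group and train one arm, so the groups can differ on it at equal blood pressure

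*Protocol article*

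**What the plan says.** Section 2.6.1 of the protocol article lists two primary outcomes: change in systolic and diastolic pressure, and "Percentage changes in the dose of antihypertensive drugs". The second of these is settled visit by visit, when "the community doctors will determine whether the dose of antihypertensive drugs needs to be adjusted". The article's stated basis for this judgement is that they make it "according to changes in blood pressure during the last month and will record the adjustment".

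Other sections describe the position of these doctors:

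- **Section 2.4.** Allocation is open: "eligible patients will enter the heat-sensitive moxibustion group or the control group according to their preferences". For those who choose moxibustion, "community doctors will further provide one-on-one training". Neither investigators nor community doctors may advise on the choice of group.
- **Section 2.5.** Control patients "will only maintain their original antihypertensive drugs and will not perform heat-sensitive moxibustion", so there is no sham. Moxibustion patients are likewise to stay on their existing drugs. The same paragraph adds: "There will be no restriction on the type and dose of antihypertensive drugs".
- **Section 2.8.** Blood pressure and dose changes are assessed at months 6 and 12. The visits at months 1–5 and 7–11 cover supplies, compliance and dose adjustment; blood pressure is not in that list. The visit schedule in Figure 2 is not reproduced in the copy at hand.
- **Section 2.10.** "Data will be collected by community doctors using pilot-tested case report forms". The only concealment described is that analysts do not see group labels.
- **Section 2.12.** Primary outcomes are analysed by intention to treat and all secondary outcomes per protocol. Effects are adjusted for baseline characteristics.
- **Section 3 (Discussion).** A positive result is expected to support moxibustion taking the place of some drug treatment.

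**The concern.** The dose outcome is not a measurement on the patient. It is a prescribing decision, and the person who decides also records the result, knows the group and has a part in delivering one of the two interventions. If doctors are somewhat readier to reduce a dose, or slower to raise one, when the patient is using moxibustion, the outcome differs between groups even if blood pressure does not.

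This is an ascertainment problem, separate from the confounding by patient preference that the Discussion admits. It enters when the outcome value is created. Hiding labels from the analysts comes too late to help, and adjusting for age, baseline pressure or drug type does not touch it.

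At stake is the claim closest to this outcome, that moxibustion could replace part of drug treatment. A lower dose in the moxibustion group could reflect the treatment, the prescriber's expectation, or both, and the data as planned could not tell them apart.

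**Working it through.** **1. What the text fixes.** Section 2.6.1 names the input to the decision (pressure change over the last month) but no procedure for turning it into a decision. Section 2.8 schedules dose adjustment in ten visits (months 1–5 and 7–11) without listing a pressure reading at them. Section 2.5 has both groups keep their original drugs, yet dose change is a primary outcome. From the article alone one cannot say on which readings, or by what common process, a dose is reviewed.

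**2. Is there a plan figure to reproduce?** No. The sample size in section 2.11 concerns systolic pressure only; no expected dose change, spread or power is given for dose. The rates below are therefore assumptions.

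**3. Illustration with no treatment effect.**

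Analysed per group: 300 × (1 − 0.20) = 240, from section 2.11.

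Assumed distribution of percentage dose change:

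- A cut is −25, −50 or −100 with equal weights: mean −58.33, mean square (625 + 2,500 + 10,000)/3 = 4,375.
- A rise is +50 or +100 with equal weights: mean 75, mean square (2,500 + 10,000)/2 = 6,250.
- All other patients have 0.

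With cut rate c and rise rate r, the mean is −58.33c + 75r and the variance is 4,375c + 6,250r − mean². For controls (c = r = 0.10) the mean is 1.67 and the variance 1,059.7.

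The standard error of the difference is √[(V₁ + V₀)/240], and the chance of two-sided P<0.05 is approximately Φ(|difference|/SE − 1.96).

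| Moxibustion cuts / rises | Variance | Difference (points) | SE | Ratio | Chance of P<0.05 |
|---|---|---|---|---|---|
| 10% / 10% | 1,059.7 | 0 | 2.97 | 0 | 5% |
| 15% / 10% | 1,279.7 | −2.9 | 3.12 | 0.93 | 15% |
| 20% / 10% | 1,482.6 | −5.8 | 3.25 | 1.79 | 43% |
| 25% / 10% | 1,668.6 | −8.75 | 3.37 | 2.60 | 74% |
| 15% / 5% | 943.8 | −6.7 | 2.89 | 2.31 | 64% |

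(The 5% and 15% entries include the small opposite tail.) Simulation with a two-sample t test agrees with every row to within about one percentage point.

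**4. A second model that contains blood pressure.** Give both arms the same systolic distribution (assumed mean 135, SD 20 mm Hg). Let a doctor make an assumed 25% cut below an assumed 130 mm Hg, and shift only the moxibustion cut-off. These values are simulation inputs and not a suggested rule. With 240 per group, shifts of 0, 2, 5 and 10 mm Hg give P<0.05 in about 5%, 13%, 59% and 99% of trials, with mean differences of about 0, −1.0, −2.5 and −4.9 points.

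Both models start from an assumed lean. They show how sensitive the outcome is to such a lean, and say nothing about whether one will occur.

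**The case against.** The strongest reply has five parts.

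- **The decision is anchored.** Section 2.6.1 ties it to recent blood pressure change, so it would be wrong to infer that doctors may set doses at will. The sentence in 2.5 about unrestricted drugs concerns permitted co-treatment and does not describe how adjustments are decided. This stands. An anchor without a common procedure still leaves room for judgement.
- **The article is condensed.** A reader might infer that no common dose-review procedure exists. The article does not support that: the full protocol, the forms and Figure 2 are not at hand, and section 2.10 mentions training in standard procedures and pilot-tested forms. This also stands. But a written procedure would reduce the problem without ending it, because the decider would still know the group and still train one arm.
- **The rates are circular.** The lean is an input, several of the leans are large relative to the 10% control rate, and section 2.12 plans adjusted analysis of covariance where the illustration uses a t test. The rates therefore show possibility only. Adjusting for baseline variables would not remove a lean that arises during follow-up.
- **Blood pressure is a check.** Cuts without a real effect would tend to raise pressure in that arm, and pressure is also primary, read from an electronic device and averaged over three readings. This is a good reason to read the two outcomes together, although small mean cuts might leave no visible trace.
- **The study is pragmatic.** Open prescribing suits that aim. It does not make a prescribing difference, taken alone, evidence of benefit.

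**Conclusion.** The concern holds in a limited form. One of the two primary outcomes is decided and recorded by doctors who know the group and train only one arm, and nothing in the planned analysis corrects a group-dependent readiness to change doses. That the doctors are unblinded is inferred from the design (open choice, no sham, personal training); the article does not use the word.

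The size of any bias cannot be derived from the article. The range of about 15% to 74% for a spurious P<0.05 rests on assumed cut and rise rates, assumed step sizes with equal weights, and 240 analysed per group. It should not be read as the trial's expected error rate.

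A reader might also infer that dose change must lose its primary status. The documents do not compel that. Done without other changes, it would do harm, because section 2.12 confines all secondary outcomes to the per-protocol population and so would add selection bias. The blood pressure outcome is not put in question by this point.

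**What to change.** 1. Reconcile sections 2.5, 2.6.1 and 2.8: whether patients keep their original drugs or have doses adjusted, at which visits, and on which blood pressure readings.
2. State that one dose-review procedure applies identically to both groups. The study clinicians should write its content before enrolment.
3. Record on the case report form, for each review, the blood pressure used and the reason for changing or not changing the dose. Report departures from the procedure by group.
4. In section 2.6.1, label dose change as an unblinded treatment decision and interpret it only jointly with the blood pressure outcome. In the Discussion, do not rest the drug-replacement statement on a dose difference alone.
5. Moving dose change to the secondary outcomes is optional. If it is moved, amend section 2.12 so that it is still analysed by intention to treat.

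The cost is protocol wording, two extra form fields, slightly less prescriber discretion and a weaker stand-alone claim about dose.
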